## Abstract

**Background:**

Distal symmetric polyneuropathy (DSPN) is the most common chronic complication of type 2 diabetes mellitus (T2DM). DSPN may lead to more serious complications, such as diabetic foot ulcer, amputation, and reduced life expectancy. Observational studies have suggested that vitamin D deficiency may be associated with the development of DSPN in T2DM. However, interventional studies have found that low-dose vitamin D supplementation does not significantly improve neuropathy in DSPN. This study aims to evaluate the efficacy and safety of intramuscular injection of high-dose vitamin D (HDVD) in T2DM with DSPN combined with vitamin D insufficiency.

**Methods and analysis:**

We will conduct a multicenter, randomized, double-blinded, and placebo-controlled trial in four large hospitals. All eligible participants will be randomly assigned to either the vitamin D_2_ supplement or placebo control group and injected intramuscularly monthly for 3 months. Additionally, anthropometric measurements and clinical data will be collected at baseline and 3 months. Adverse events will be collected at 1, 2, and 3 months. The primary outcome measure is the change in the mean Michigan Neuropathy Screening Instrument (MNSI) score at baseline and 3 months post-intervention. We will use the gold-standard liquid chromatography-tandem mass spectrometry method to distinguish between 25(OH)D_2_ and 25(OH)D_3_ levels. The MNSN score before the intervention will be used as a covariate to compare the changes between both groups before and after the intervention, and the analysis of covariance will be used to analyze the change in the MNSI score after HDVD supplementation.

**Discussion:**

Glycemic control alone does not prevent the progression of DSPN in T2DM. Some studies have suggested that vitamin D may improve DSPN; however, the exact dose, method, and duration of vitamin D supplementation are unknown. Additionally, neuropathy repair requires HDVD supplementation to sustain adequate vitamin D levels. This once-a-month intramuscular method avoids daily medication; therefore, compliance is high. This study will be the first randomized controlled trial in China to analyze the efficacy and safety of HDVD supplementation for patients with T2DM and DSPN and will provide new ideas for pharmacological research and clinical treatment of diabetic neuropathy.

**Clinical trial registration:**

https://www.chictr.org.cn/, identifier ChiCTR2200062266.

## Introduction

1

According to the latest International Diabetes Federation statistics for 2021, the total number of people with diabetes worldwide is 536.6 million—and China accounts for a quarter (1). The prevalence of diabetes among adults in China is 12.8%, higher than the global average of 10.5%. Moreover, the number of people with diabetes in China is approximately 129.8 million, and those with type 2 diabetes mellitus (T2DM) account for > 90%. Therefore, T2DM is a serious public health problem in China (2). Additionally, the chronic complications caused by T2DM are a threat to national health. Notably, the complications involving peripheral nerves—peripheral neuropathy—can affect 75% of people with T2DM. Peripheral neuropathy occurs as early as in the pre-diabetic state of obesity, indicating its close relation to diabetes, obesity, and other metabolic diseases (3, 4).

Distal symmetrical polyneuropathy (DSPN) is the most representative manifestation of nerve damage in T2DM and is more common than other spinal nerves, cranial nerves, and autonomic neuropathy lesions (5). DSPN develops slowly, starting with small nerve fibers at the end of the limb and progressing to larger nerves, including sensory and motor nerves. The symmetrical onset of numbness and sensory abnormalities is the earliest clinical symptom in many patients with DSPNs. Moreover, approximately one-third of patients experience burning, pin and needle sensations, and pain. These painful symptoms are unbearable and lead to insomnia and depression, reducing patients’ quality of life (6, 7). Additionally, patients with DSPN are prone to complications, such as diabetic foot ulcers, due to a long-term lack of self-sensory protection, leading to serious complications, such as irreversible amputation and shortened life expectancy. Finally, as the disease progresses, people’s ability to work becomes severely affected, causing a serious economic burden and wastage of resources for individuals, families, and society; therefore, DSPN requires more attention (8, 9).

The clinical efficacy of DSPN treatment is poor. The Action to Control Cardiovascular Risk in Diabetes (ACCORD) study showed that glycemic control alone in T2DM does not reduce the incidence of DSPN, suggesting that hyperglycemia is not the only factor influencing the development of DSPN. Recently, clinicians have been looking for alternative treatments to improve DSPN (10). The etiology and pathogenesis of DSPN have not been elucidated; however, its development involves or is accelerated by abnormal insulin signaling pathways, microcirculatory disorders, non-enzymatic advanced glycosylation end product pathways, oxidative stress, and other factors leading to mitochondrial dysfunction, DNA damage, and apoptosis (9, 11).

Vitamin D is a fat-soluble ring-opening steroid discovered over 100 years ago and includes vitamin D_2_ (ergocalciferol) and D_3_ (cholecalciferol). Vitamin D_2_ is derived from foods, such as mushrooms, offal, egg yolks, and fatty sea fish. Vitamin D_3_ is converted from 7-dehydrocholesterol in the skin by ultraviolet light. Vitamins D_2_ or D_3_ require two hydroxylation processes, mediated by 25-hydroxylase in the liver and 1α-hydroxylase in the kidneys, to become active as 1,25-(OH)_2_D_2_ or 1,25-(OH)_2_D_3_, respectively. At present, activated vitamin D has gone beyond the traditional concept of vitamin and as it can play a hormone-like role, so 1,25-(OH)_2_D is also known as D hormone. Therefore, some scholars refer to the unactuated form of vitamin D as a D prohormone. Additionally, activated vitamin D is directly involved in gene regulation *via* the vitamin D receptor (VDR), which has several biological roles. Since vitamin D receptors are found in bones, kidneys, parathyroid glands, small intestine, nerve tissue, and pancreatic β-cell, vitamin D may have other biological roles in addition to its traditional role of regulating calcium, phosphorus, and bone metabolism. These roles include facilitating cell differentiation and proliferation, reducing superoxide, regulating lipid metabolism and inflammatory factors, reducing superoxide, promoting nerve growth factors, regulating immunity, reducing cytokine storms, and reducing COVID-2019 mortality (12–16).

Considering all these functions, vitamin D is important for health; however, its insufficiency is a widespread public health problem. Vitamin D nutritional status is determined by measuring serum 25-(OH)D levels—a sum of 25-(OH)D_2_ and 25-(OH)D_3_. The Endocrine Society recommends a 25-(OH)D level of 30 ng/mL (17); a patient is considered to have a vitamin D -insufficient state if this level is not reached (17–19). Studies have shown that vitamin D deficiency occurs in 74.7% of people with T2DM and affects people with prediabetes. Moreover, studies have shown that people with low vitamin D levels and prediabetes have a significantly higher risk of developing diabetes (20, 21).

A study by the National Health and Nutrition Examination Survey showed that the risk of developing DSPN increases by 2.59 times in people with vitamin D deficiency (22). Another study suggested that vitamin D deficiency may be an independent risk factor for DSPN (23). In an observational study, Seham et al. (24) found that vitamin D levels were significantly lower in patients and DSPN than in those with T2DM without DSPN and confirmed that 87.6% of those with DSPN had vitamin D deficiency, and the prevalence of vitamin D deficiency in T2DM without DSPN was only 45%.

However, the mechanisms by which vitamin D deficiency specifically affects DSPN are unknown. Vitamin D may improve glycemic control by promoting β-cell secretion and increasing insulin sensitivity. Additionally, vitamin D may reduce oxidative stress and prevent nerve damage (25). Animal studies have shown that vitamin D increases the synthesis of nerve growth factors in rats (26). Vitamin D is a potent inducer of neurotransmitters and can reduce nerve demyelination and improve axonal regeneration (27, 28).

A meta-analysis showed that vitamin D supplementation effectively reduced neuropathic pain and prevented further nerve damage (29). The association between vitamin D and pain may be due to nociceptive calcitonin gene-related peptide (CGRP)-positive neurons. These neurons have a distinct vitamin D phenotype, and their ligands and receptors are hormonally regulated. A study reported that vitamin D receptor expression in the growth cones and CGRP expression increased rapidly with vitamin D deficiency, indicating a possible connection between vitamin D and pain. Additionally, this study suggested the presence of lower pain tolerance in patients with vitamin D deficiency (30, 31).

Adequate vitamin D levels are not achieved with sunlight and food intake alone; therefore, additional supplements are required. Studies have shown that different doses of vitamin D supplementation may produce different results in DSPN treatment. A clinical study by Karonova et al. (32) showed that high-dose vitamin D (HDVD) supplementation in patients with DSPN and vitamin D deficiency achieved adequate status in all patients; however, only half of the low-dose group achieved adequate status. Moreover, the severity of neuropathy was accompanied by a significant reduction in inflammatory markers in the HDVD group; however, these markers were not altered in the low-dose group. Basit et al. (33) showed a significant decrease in total pain score and a reduction in positive symptoms in diabetic neuropathy patients treated with HDVD. Silva et al. (34) treated patients who had diabetic cardiac autonomic neuropathy with HDVD and showed significant improvement in parameters related to resting heart rate variability without adverse effects. Notably, neuropathy repair and symptom improvement are slow; therefore, we decided to use HDVD supplementation to repair neuropathy.

It is currently believed that vitamin D_2_ and D_3_ supplementation have the same effect of correcting vitamin D insufficiency, and it is believed that injection is better than oral supplementation (17, 35). Indeed, lower daily doses of vitamin D supplements require longer time to increase vitamin D levels in the body and are less likely to sustain sufficient levels. In addition, daily medication reduced compliance and executive function in patients, thereby reducing the number of people who reach sufficient state of vitamin D. Therefore, some scholars have proposed that the injection of HDVD supplementation as a method of administration with lower frequency and longer interval will be more conducive to obtain desired intervention outcomes (36, 37). Compared to vitamin D_3_, vitamin D_2_ has a lower binding affinity to vitamin D-binding proteins (VDBP). This means that taking vitamin D_2_ instead of vitamin D_3_ will result in higher levels of free vitamin D concentration in the blood, which will bind better to VDR (38, 39). Indeed, vitamin D_2_ has been used clinically for more than 50 years (39). Therefore, we use vitamin D_2_ injection as a strategy to correct vitamin D insufficiency.

The traditional nerve conduction test reflects only the lesions of large nerve fibers but not those of small fibers, such as fine myelinated A δ, unmyelinated C, and autonomic nerve fibers, which mediate nociceptive pain and temperature perception (5). Michigan Neuropathy Screening Instrument (MNSI) comprises a questionnaire and physical examination. The questionnaire contains 15 questions that address DSPN symptoms, with a maximum score of 13 points, and is completed by the patients. The physical examination is performed by the physician and includes ankle reflexes, vibration perception, foot ulceration, and feet appearance. Physical examination has a maximum score of 8 points for both feet. Multiple studies have demonstrated that MNSI is a reliable and effective tool for assessing DSPN. Additionally, compared with nerve conduction tests, MNSI avoids invasive examinations and the discomfort of electrical stimulation. Moreover, MNSI may avoid missing early small-fiber lesions in DSPN (40–44). Therefore, we will use the MNSI to assess the changes in neuropathy after HDVD supplementation.

The development of DSPN is relatively reversible in the early stage; however, it becomes a refractory nerve injury in the later stage, and the condition is persistent and recurrent. Correcting vitamin D deficiency helps prevent and treat DSPN. However, the specific dosage, long-term treatment effects, and related side effects should be confirmed in high-quality randomized controlled trials. Few clinical trials have investigated the effects of vitamin D supplementation on neuropathy in China’s population with DSPN and T2DM. Therefore, this study aims to explore the efficacy of HDVD supplementation in treating DSPN in T2DM, assess its safety, and collect information on adverse reactions.

## Methods and analysis

2

### Study design

2.1

We will conduct a multicenter, prospective, randomized, double-blinded, and placebo-controlled clinical trial. First, participants will be assigned to the HDVD supplementation or placebo control group in a 1:1 block randomization scheme. Next, intramuscular injections will be administered at baseline and 1 and 2 months later. Moreover, we will collect anthropometric measurement data, fasting blood glucose, β-cell function, hemoglobin A1c, and other biochemical data. Lastly, MNSI will be performed at baseline and 3 months later. This study will follow the Comprehensive Reporting Test Standard Guidelines (45). The study flow chart is shown in **Figure 1**.

**Figure 1 f1:**
[figure not shown]
Trial flow chart.

#### Study setting

2.1.1

We will recruit participants from four large hospitals: Longyan First Affiliated Hospital of Fujian Medical University, Longyan Traditional Chinese Medicine Affiliated Hospital of Fujian University of Traditional Chinese Medicine, Longyan Boai Hospital, and Longyan Shanghang County Hospital. All participants will provide written informed consent to participate in the study.

#### Participants

2.1.2

The inclusion and exclusion criteria for the target participants are listed in **Table 1**. All diagnostic criteria will be based on the guidelines and expert consensus of the World Health Organization and China. To recruit as many eligible patients with DSPN as possible, we will distribute recruitment leaflets to outpatients and hospital wards and release recruitment information using the WeChat mobile application (version 8.0.32, Tencent Holdings Limited, Shenzhen, China) and other online forms. Those interested can contact the recruiter directly *via* phone. If a participant experiences a serious adverse event or disease (such as anaphylactic shock or myocardial infarction) during the trial, whether related to the investigational drug or not, the person will be treated immediately and withdrawn from the trial. Moreover, the participants will be allowed to withdraw from the trial at any time.

**Table 1 T1:** Inclusion criteria and exclusion criteria.

Inclusion criteria	Exclusion criteria
1. All participants live permanently in Longyan City, South China (latitude and longitude 115 ° 50 ′ 56 "-117 °44 ′ 15" E, 24 ° 22 ′ 31 "-26 °2 ′ 35" N).	1. Patients without glucose homeostasis such as diabetic ketoacidosis and hypoglycemia.
2. Aged between 20 and 79 years.	2. Patients with hyperthyroidism, hypothyroidism, or parathyroid disease.
3. 25(OH) vitamin D < 30 ng/mL	3. Severe disability or mental illness and pregnant and lactating women.
4. All participants will sign a written informed consent form.	4. Alcoholic or drug abusers, a vegetarian who never eats fish or meat.
5. The diagnosis of type 2 diabetes mellitus will be confirmed according to the diagnostic criteria of the World Health Organization in 1999.	5. Chronic gastrointestinal diseases such as intestinal tuberculosis, ulcerative colitis, or irritable bowel syndrome.
6. The diagnosis of distal symmetric polyneuropathy will be diagnosed according to the Guidelines for the Prevention and Treatment of Type 2 Diabetes Mellitus in China (2020 Edition). Five neurological examinations will be performed, including ankle reflexes, pinprick pain, vibration, pressure, and temperature sensations. If a patient has one clinical symptom (numbness, pain, and paresthesia) and any of the five neurological examinations are abnormal, the patient will be diagnosed with DSPN. Additionally, patients will be diagnosed with DSPN if two of the five neurological examinations are abnormal, without any clinical symptoms, **Figure 2**.	6. The participant has recently taken the following medications or supplements: immunosuppressants or glucocorticoids, such as prednisone at doses >10 mg/day; drugs such as phenytoin sodium, phenobarbital, and rifampicin that may affect the catabolism of vitamin D; vitamin D or active vitamin D, such as calcitriol; and drugs that directly affect nerves (such as chemotherapy drugs, vitamin B6 or Neurobion). 7. Patients with large areas of skin pigmentation or skin diseases. Those who engage in long-term outdoor activities or have tropical tourism plans in the next 3 months. Using sunscreen on the face and hands 8. Hyperphosphatemia and renal rickets.
	9. Blood calcium level >11 mg/dL (2.75 mmol/L), history of urinary tract stones, and sarcoidosis.
	10. Acute stress diseases, such as shortness of breath, fever and diarrhea, severe leukopenia, malignant tumor, liver dysfunction (bilirubin> 1.5 times the upper limit of normal value, alanine aminotransferase> 2 times the upper limit of normal value) or organic diseases, such as decreased renal function eGFR*<20 mL/min/1.73 m2.
	11. Neuropathy caused by other causes, such as cervical and lumbar lesions (nerve root compression, spinal stenosis, cervical and lumbar degeneration), cerebral infarction, Guillain–Barre syndrome, and serious arteriovenous vascular lesions (venous embolism, lymphangitis).
	12. Participants considered unsuitable for the study based on the investigator's judgment.

DSPN, Distal symmetric polyneuropathy; eGFR, estimated glomerular filtration rate.

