### Intervention

2.3

All participants will receive diabetes health education and follow-up. Medical nutrition therapy will be recommended for every patient with diabetes, and they will be advised to avoid overeating and undereating, which causes oxidative stress due to glucose fluctuations, exacerbating peripheral nerve damage. Moreover, self-monitoring of blood glucose will be recommended for every participant. The optimal blood glucose control target will be 4.4 mmol/L < fasting blood glucose < 7.0 mmol/L, 2-h postprandial blood glucose < 10.0 mmol/L, and avoid hypoglycemia. Next, exercise therapy, avoidance of foot injuries, and wearing white socks frequently will be recommended for every patient with diabetes to detect minor local injuries early.

After randomization, all participants will receive an intramuscular injection of the trial drug (vitamin D_2_ 600,000 units, 3 mL, monthly for 3 months) or placebo (0.09% sodium chloride 0.0027 g, 3 mL, monthly for 3 months) into the gluteus maximus. Vitamin D_2_ is produced by Jiangxi Gannan Haixin Pharmaceutical Co. Ltd. (Ganzhou, Jiangxi, China), and sodium chloride by Hubei Xinghua Pharmaceutical Co. Ltd. (Wuhan, Hubei, China). Each injection will be packaged in an opaque sealed package with an instruction leaflet and label. Drug dispensing will be performed by a third person independent of the implementer and participant. It is critical that all participants remain in the follow-up cohort as long as possible, and the efforts of all investigators and related personnel will improve participant adherence to the intervention and follow-up schedule. If the participant refuses to continue the follow-up, the investigator will determine the reason and encourage the participant to continue the intervention and follow-up.

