#### Safety assessment and adverse events reporting

2.4.4

We will evaluate liver function, albumin, renal function, calcium, phosphorus, potassium, sodium, chloride, and other biochemical parameters at baseline and post-intervention to evaluate the safety of the HDVD. All adverse events reported during the study will be closely monitored and recorded. In this trial, an adverse event is any unfavorable or unexpected occurrence related to the intervention. The investigator will ask the participants questions regarding adverse reactions. Participants will be called on days 1, 3, and 7 after each injection to determine any adverse events (**Table 3**). Moreover, participants will be asked to self-report any adverse events at any time. All adverse events will be professionally addressed, closely monitored by a physician, and treated as necessary. Serious adverse events will be reported to the study director—responsible for managing adverse reaction reports—within 1 h. Additionally, related serious adverse events will be reported to the Ethics Committee of Longyan First Affiliated Hospital of Fujian Medical University. The Ethics Committee is independent of the investigators, and the investigators are not members of the Ethics Committee.

**Table 3 T3:** Safety assessment and adverse event follow-up of participant.

	M0	M1	M2	M3
Liver function: alanine aminotransferase, aspartate aminotransferase, total bilirubin, albumin, globulin	√			√
Renal function: creatinine, blood urea nitrogen, and eGFR calculated by the CKD-EPI equation	√			√
Creatine kinase (CK), creatine kinase myocardial band (CK-MB), lactate dehydrogenase (LDH), alkaline phosphatase (ALP)	√			√
Electrolytes: calcium (Ca), phosphorus(P), potassium(K), magnesium (Mg), sodium (Na), chloride (Cl)	√			√
Closely follow up on the physical health after injection, and receive consultation and feedback at any time within 24 h	√	√	√	√
Did the participant experience any adverse reactions after the injection (whether or not determined to be related to this injection)	√	√	√	√
Digestive adverse reactions: decreased appetite, constipation or diarrhea, abdominal pain, nausea, or vomiting	√	√	√	√
Skin adverse reactions: pruritus, allergic dermatitis, rash, swelling, and pain at the injection site	√	√	√	√
Nervous system adverse reactions: metallic sensation in the mouth, persistent headache, convulsions, and insomnia	√	√	√	√
Urinary adverse reactions: cloudy urine, nocturnal polyuria, and hematuria	√	√	√	√

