### Data analysis

2.6

Any participant who completes the randomization will be included in the intention-to-treat set for data analysis. In cases when random or unforeseeable missing data occur, the missing data will be processed by multiple imputation method and sensitivity analysis will be carried out (49). The safety set which contains at least one safety assessment and adverse event report will be used to analyze the safety of HDVD supplementation. Quantile-quantile plot will be used to determine if the data conforms to a normal distribution. For descriptive analysis, the results of continuous variables (age and body mass index, among others) that conform to normal distribution will be expressed as mean ± standard deviation, and those that do not conform to normal distribution will be expressed as median and interquartile range. Categorical variables (sex and smoking status) will be expressed as frequencies and percentages.

Baseline data will be compared between the HDVD supplementation and placebo control groups. In HDVD supplementation or placebo control group, a paired sample t-test will be used for post-intervention versus pre-intervention comparisons. The difference value of MNSI before and after intervention will be performed by independent sample t-test test to compare the difference between the two groups. If the data does not conform to normal distribution, the Mann-Whitney U test will be used for analysis. The chi-square test will be used for categorical variables.

Furthermore, we will use the MNSI score before intervention as a covariate, and the F value will be calculated using analysis of covariance (ANCOVA) to analyze the change in the MNSI score after HDVD supplementation. Finally, if the number of adverse events occurring during the study is sufficient, the chi-square test or Fisher’s exact probability method will be used to compare differences in adverse events between both groups.

All data will be analyzed using the R software (version 4.1.2; R Foundation for Statistical Computing, Vienna, Austria). Additionally, all statistical analyses will be performed using a two-sided test, considering P < 0.05 statistically significant.

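### A serious adverse event, related or not, ends trial participation and not only injections, so anyone withdrawn before month 3 has no scheduled post-baseline MNSI, calcium or renal value

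*Protocol article*

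**What the plan says.** Section 2.1.2 (Participants) sets the rule for a serious adverse event or disease, with anaphylactic shock and myocardial infarction as examples: "whether related to the investigational drug or not, the person will be treated immediately and withdrawn from the trial". The next sentence uses the same phrase for voluntary exit: "the participants will be allowed to withdraw from the trial at any time".

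The assessments that this touches are scheduled as follows.
- **Primary outcome.** Section 2.1 (Study design): "MNSI will be performed at baseline and 3 months later". Table 2 ticks the MNSI at M0 and M3 only.
- **Laboratory safety.** Section 2.4.4 schedules liver function, renal function, electrolytes "and other biochemical parameters at baseline and post-intervention to evaluate the safety of the HDVD". Table 3 ticks calcium, creatinine and eGFR at M0 and M3 only.
- **Months 1 and 2.** Injections, health education and adverse event questions, with no MNSI and no laboratory tests.

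On retention, section 2.3 (Intervention) states: "It is critical that all participants remain in the follow-up cohort as long as possible". For a participant who refuses further follow-up, "the investigator will determine the reason and encourage the participant to continue the intervention and follow-up".

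On analysis, section 2.6 states: "Any participant who completes the randomization will be included in the intention-to-treat set for data analysis". It continues: "In cases when random or unforeseeable missing data occur, the missing data will be processed by multiple imputation method", and the same sentence adds that a sensitivity analysis will be done.

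**The concern.** Stopping a drug and leaving a trial are different things. Stopping injections after a serious event protects the participant. Ending follow-up as well adds no protection, and it discards data from people whose outcome and laboratory values matter to the comparison. The wording of section 2.1.2 does both at once, and does so even when the event has nothing to do with the injection.

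Two things are at stake. First, the missing values would be produced by a protocol rule and would follow a clinical event, so their absence may depend on treatment. Second, safety is a stated aim. The regimen is 600,000 units monthly for three months, and the Discussion promises data on changes in renal function and blood calcium while conceding that earlier safety studies were small. A scheduled M3 calcium or renal result after a serious event is among the more informative values that the trial could collect.

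**Working it through.** **Step 1. What the schedule leaves after withdrawal.** Reading Tables 2 and 3 against the rule:

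| Time of event | Scheduled post-baseline MNSI | Scheduled post-baseline calcium and renal values | Event recorded |
|---|---|---|---|
| Before M3 | 0 | 0 | yes |
| At or after the M3 assessment | 1 | 1 | yes |

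The shown text has no early-termination assessment to fill the first row. Unscheduled tests during clinical care are possible but not assured.

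**Step 2. Reproduce the plan's sample size.** Inputs from section 2.1.3: difference 1.19, SD 1.29, two-sided alpha 0.01, power 0.95. Allocation is 1:1 (section 2.1).

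n per group = 2 × (2.576 + 1.645)² × (1.29/1.19)² = 41.9, rounded up to 42, so 84 in total. With 20% loss, 42/0.80 = 52.5, rounded up to 53, so 106 in total. Both figures match the article.

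**Step 3. Size of the loss.** The documents give no serious event rate, so the counts here are assumptions: 1, 2 or 4 participants withdrawn before M3, all from one arm of 53.

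- Share of that arm without M3 data: 1/53 = 1.9%, 2/53 = 3.8%, 4/53 = 7.5%.
- Power of the two-sample t-test (noncentral t), with d = 1.19/1.29 = 0.922, noncentrality d/√(1/n₁ + 1/n₂), n₁ + n₂ − 2 degrees of freedom and two-sided alpha 0.01:

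| Withdrawn from one arm | No other loss | After the full 20% loss |
|---|---|---|
| 0 | 53 v 53: 98.2% | 42 v 42: 94.1% |
| 1 | 52 v 53: 98.1% | 41 v 42: 93.8% |
| 2 | 51 v 53: 98.0% | 40 v 42: 93.5% |
| 4 | 49 v 53: 97.7% | 38 v 42: 92.7% |

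The 94.1% at 42 v 42 is slightly below the planned 95% because the t-test is used here in place of the normal approximation.

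Section 2.6 tests at P < 0.05. At alpha 0.05 the same calculation gives 99.7% (53 v 53), 99.6% (49 v 53), 98.7% (42 v 42) and 98.3% (38 v 42). If the withdrawals fall inside the 20% allowance, planned power does not change.

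**Step 4. Safety.** No figure can be derived. It would need event counts by arm and the laboratory values themselves.

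**The case against.** The strongest reply is that section 2.1.2 does not forbid an M3 assessment, and that a journal article may leave the definition of withdrawal, and any early-termination visit, to a full protocol that is not shown. That is fair as far as it goes, and the full protocol may well be narrower. But the sentence is a positive instruction, not a gap. It names the trial and not the injections, and it shares its wording with voluntary exit. A site that follows it as written would stop follow-up.

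A reader might infer that the rule contradicts the intention-to-treat analysis. It does not. The set is defined by randomisation, withdrawn participants stay in it, and imputation exists for those without a measured value. A reader might also infer a direct conflict with section 2.3. That is too strong as well: the encouragement clause covers people who refuse follow-up, and a general retention aim can stand beside a safety exception. The rule sits uneasily with both; it does not contradict either.

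It would also be wrong to say that missing data are left unaddressed. Multiple imputation and a sensitivity analysis are both planned. The article words imputation for random or unforeseeable gaps. Whether a withdrawal required by rule fits that wording is debatable, since the rule is foreseeable but an individual infarction is not. Little turns on this: no imputation recovers a value that could have been measured.

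Nor is the safety signal itself lost. Section 2.4.4 has events monitored by a physician and serious ones reported to the study director within 1 h, with calls on days 1, 3 and 7 after each injection. This stands, and it limits the loss to the scheduled M3 measurements.

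**Conclusion.** The point holds as a minor one. As written, the rule removes from scheduled follow-up anyone with a serious event before M3, whatever its cause, and leaves no scheduled post-baseline MNSI, calcium or renal value for that person.

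The effect on power is negligible: at most 0.5 percentage points from 53 per arm and 1.4 points from 42 per arm at alpha 0.01. Both figures rest on assumed counts of up to 4 withdrawals, all in one arm. The true number is unknown and may be zero. The substantive loss is outcome and safety data after serious events, where missingness may depend on treatment; its size cannot be derived from the documents. The conclusion assumes that the full protocol does not define withdrawal more narrowly than the article does.

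**What to change.** Reword the sentence in section 2.1.2 along these lines: after a serious adverse event the participant is treated immediately and injections are stopped where clinically indicated, but the participant remains in follow-up for the M3 MNSI, the Table 3 laboratory tests and adverse event follow-up unless consent is withdrawn. Analyse these data in the intention-to-treat and safety sets that section 2.6 already defines, and impute only what is still missing.

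The cost is one protocol sentence, a matching statement in the consent form, and a few M3 visits that are already on the schedule. Some participants will be too ill to attend, so the change reduces the missing data but does not remove it.
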